**6. [Basis for scientific rationality of research]**

If this study proves that yokukansan is effective for perioperative anxiety and pain, it will be possible to improve the patient's perioperative quality of life with inexpensive Chinese herbs with few side effects.

**7. [Procedures for receiving informed consent, etc.]**

To explain the research, use the research manual (attached to the materials) to participate in the clinical research, regarding the purpose, method and funding source of the clinical research, possible conflicts of interest, involvement with related organizations such as researchers, and so on. A written and oral explanation of the expected benefits and possible risks, the inevitable unpleasant condition, the response after the end of the clinical study, the presence or absence of compensation for the clinical study, and other necessary matters. Please sign the attached material). Strict privacy is maintained for the patient, participation in the study is not obligatory, refusal to participate in the study, or withdrawal of consent in the middle does not disadvantage the subsequent treatment. Explain the warranty. When a participant withdraws his / her consent, he / she confirms his / her intention to withdraw his / her consent by using the consent withdrawal form (attached to the material).

**8. [Handling of personal information, etc.]**

All persons in charge of this study shall comply with the "Declaration of Helsinki (revised in October 2013)" and the Clinical Research Law. When publishing the results of the study, do not include information that can identify the subject. In addition, we will not use the materials of the subjects obtained in the research other than the purpose of the research.

**9. [Burden on research subjects and expected risks and benefits, comprehensive evaluation of these, and measures to minimize the burden and risks]**

Patients in the control group of this study do not take any medication and therefore do not suffer any benefit or disadvantage. On the other hand, patients in the intervention group have the disadvantages of having to take the drug even if it is difficult to take it, and the side effects of Chinese herbs may occur.

The side effects of yokukansan have been reported to be hypokalemia, gastrointestinal disorders (diarrhea and nausea), liver dysfunction, etc., but the frequency is stated to be less than 0.1-5% in the package insert. All of them are side effects of long-term continuous use (reported in 13 days at the earliest). Most of them occur in the elderly aged 65 and over. Since this time, the drug was taken only twice, it is highly unlikely that such side effects will occur. In the unlikely event that yokukansan causes health problems, the researcher will deal with it in good faith and provide appropriate medical care. The cost will be covered by the subject's insurance, and no special compensation will be provided by this study. The collection period for adverse events should be continuous from the acquisition of consent to the end of the study.

**10. [Procedures for collecting, recording, and reporting information on diseases, etc. (including identification of important diseases, etc. that the principal investigator should report to the principal investigator and abnormal values ​​of clinical tests, and requirements and deadlines for reporting) and outbreaks of diseases, etc. Observation period of subjects for later clinical studies]**

As described in the above, the onset of serious complications due to oral administration of Suppression and the appearance of abnormal values ​​in clinical tests are not expected, but complications with clinical symptoms (eg, weakness due to hypokemia, etc.) ), If the length of hospital stay due to breast surgery set by the clinical pass is extended, information will be transmitted from the Niigata University Medical and Dental Hospital and Niigata Prefectural Cancer Center Niigata Hospital Breast Surgery to the doctors in charge of anesthesia at each hospital, and they will be discharged. Until then, the progress of clinical symptoms and test results is observed and recorded.

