**4. [Research method and period]**

① Research implementation period

From November 1, 2017 to March 31, 2021.

② Information on drugs used

Name: Tsumura Yokukansan (Product number: 054)

Route of administration, dosage and administration: Oral, 1 packet (2.5 g) at a time

Dosage form: Extract granules

③ Research subjects

Patients aged 20 to 60 years who undergo breast cancer surgery at Niigata University Medical and Dental Hospital or Niigata Prefectural Cancer Center Niigata Hospital and undergo total mastectomy and sentinel lymph node biopsy, or partial mastectomy and sentinel lymph node biopsy (Details will be described later).

④ Research method

Multicenter / Open Label / Superiority test by forced random sampling

[1] A pre-treatment questionnaire survey will be conducted on all subjects, and the age, BMI, surgical history, and general status (American Society of Anesthesiologists-Physical Status: ASA-PS, ECOG-PS) will be recorded in advance. Also, before taking the study drug, record the measurement of amylase in saliva, the Hospital anxiety and depression scale (HADS), and the State Trait Anxiety Inventory (STAI).

[2] Subjects are assigned to two groups, one with yokukansan (intervention) and the other without (control), according to the results of randomization. The intervention group should be given 1 packet (2.5 g) of TSUMURA Yokukansan before sleep on the day before surgery and 1 packet (2.5 g) 2 hours before entering the operating room on the day of surgery. For the purpose of maintaining the same quality between the two groups, a forced allocation algorithm is created, and if a bias is confirmed between the groups, forced allocation is performed based on age, surgical history, etc.

[3] Subjects in the intervention group take 1 packet of yokukansan orally 2 hours before entering the operating room on the day of surgery, and then all participants are measured salivary amylase in the operating room. Anesthetized by general anesthesia in the operating room and undergo total or partial mastectomy and sentinel lymph node biopsy

[4] Record salivary amylase measurements, HADS, STAI, visual analog scale of pain: VAS, QOR (Quality of recovery), and the presence or absence of analgesic use 24 hours after surgery.

| 24-hour before surgery | Salivary amylase  HADS STAI |
| --- | --- |
| Just before surgery | Salivary amylase |

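### Section 9 asks for continuous adverse-event collection, but section 10 only triggers it and the schedule has no adverse-event item, so the named side effects are not collected systematically

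*Protocol*

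**What the plan says.** Protocol section 9 lists the known risks of yokukansan: "hypokalemia, gastrointestinal disorders (diarrhea and nausea), liver dysfunction, etc., but the frequency is stated to be less than 0.1-5% in the package insert". It attributes them to long-term use, 13 days at the earliest and mostly at age 65 and over, and considers them very unlikely after two doses. It then sets the collection rule: "The collection period for adverse events should be continuous from the acquisition of consent to the end of the study".

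Section 10 gives the procedure. After stating that serious complications and abnormal laboratory values are not expected, it turns to "complications with clinical symptoms (eg, weakness due to hypokemia, etc" and then continues: "If the length of hospital stay due to breast surgery set by the clinical pass is extended, information will be transmitted". The information passes from breast surgery to the anesthesia doctors at each hospital, and the end point is discharge: "Until then, the progress of clinical symptoms and test results is observed and recorded".

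The postoperative assessment in section 4 reads: "Record salivary amylase measurements, HADS, STAI, visual analog scale of pain: VAS, QOR (Quality of recovery), and the presence or absence of analgesic use". The endpoint list in the same section has salivary amylase as primary and HADS, STAI, QOR and pain VAS as secondary. Section 13 separately requires a prompt written report of any serious adverse event that comes to the investigators' attention.

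**The concern.** Continuous collection and triggered notification are different rules. A site that follows section 10 waits until breast surgery notices something and passes it on; a site that follows section 9 looks for events in everyone from consent onward. Two hospitals take part, so the two rules could be applied differently within one trial.

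At stake is the non-serious safety record. Nausea after general anesthesia is hard to interpret without the same record in untreated patients. In an open-label trial, what staff choose to pass on without being asked may depend on the known allocation. An almost empty record could then reflect how events were picked up rather than how often they occurred. An analysis plan cannot repair this afterwards, because it cannot recover events that were never collected.

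**Working it through.** **Step 1: the two rules side by side.**

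| | Section 9 | Section 10 |
|---|---|---|
| Start | consent | when a trigger occurs |
| Mode | continuous | notification by breast surgery |
| Condition | none | symptomatic complication and/or prolonged stay |
| End | end of the study (not defined per patient) | discharge |

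Start, mode and condition differ on any reading. The end differs only on some readings. If the end of the study means the close of the research period (March 31, 2021), discharge is earlier. If it means a patient's last assessment (24 hours after surgery, with a tolerance of 12 hours), follow-up to discharge may be as long or longer.

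**Step 2: what each named side effect needs in order to be recorded.** The section 10 sentence is damaged, so both readings are shown.

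| Event | Triggers are alternatives | Both triggers required |
|---|---|---|
| Low potassium or liver abnormality, no symptoms, normal stay | not notified | not notified |
| Nausea or diarrhea, normal stay | notified if regarded as a complication | not notified |
| Symptomatic event with prolonged stay | notified | notified |

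The first row is missed on either reading; the second depends on the reading.

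**Step 3: does the schedule fill the gap?** The section 4 list has no adverse-event question, no potassium or liver test and no gastrointestinal item. QOR is named as an efficacy endpoint; the protocol does not describe its items or use it as an adverse-event record.

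**Step 4: what complete recording could show.** The planned size is about 40 per group. It reproduces from 80% power, two-sided 0.05, 75% success with yokukansan and, as an assumption, 45% in controls (reading the stated 0.3 as an absolute difference). With mean rate 0.60:

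n = [1.96 × √(2 × 0.60 × 0.40) + 0.8416 × √(0.75 × 0.25 + 0.45 × 0.55)]² / 0.30² = 40.7, so 41.

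Chance of at least one event among 40 treated patients, 1 − (1 − p)^40, across the range quoted in section 9:
- p = 0.1%: 1 − 0.999^40 = 3.9%
- p = 1%: 1 − 0.99^40 = 33.1%
- p = 5%: 1 − 0.95^40 = 87.1%

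Exact upper 95% limit after 0 of 40: two-sided 1 − 0.025^(1/40) = 8.8%; one-sided 1 − 0.05^(1/40) = 7.2%. Both exceed the 5% at the top of the quoted range.

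Comparing 5% with 1% (illustrative rates) at 40 per arm has about 18% power by the normal approximation, and 285 per arm would be needed for 80%. A comparison between arms could therefore only be descriptive.

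**The case against.** The strongest reply is that section 9 already states the collection rule for all patients, and section 10 merely describes the follow-up of notified cases. On that view the sections complement each other. Serious events are covered by section 13 without limit by arm, cause or discharge. With two doses in patients aged 20 to 60, few events are expected. The analysis of adverse events may also sit in a statistical analysis plan that is not at hand.

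Much of this stands. Serious events are covered. The end-date conflict depends on an undefined term. Once a trigger occurs, symptoms and test results are recorded, so the side effects are not wholly unmeasured. The absence of a by-arm analysis cannot be held against the protocol. What does not stand is that section 9 is thereby put into practice: it names no question, form or visit, and neither does the section 4 schedule.

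A reader might infer three stronger points that the protocol does not support:
- **Recording depends on attribution to yokukansan.** The reference to oral administration belongs to the clause about what is not expected. The triggers are symptoms and length of stay, and hypokalemic weakness is only an example.
- **Events in controls would go unrecorded.** Section 9 does say "Patients in the control group of this study do not take any medication and therefore do not suffer any benefit or disadvantage", but this concerns the burden of participation. Neither the collection rule nor the triggers are limited by arm. What remains is the open-label risk of uneven unsolicited reporting.
- **Section 6 plans a safety conclusion.** Its phrase "inexpensive Chinese herbs with few side effects" is a background remark about the drug, conditional on efficacy. No safety hypothesis or endpoint is stated.

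**Conclusion.** The point holds as a mismatch between two stated rules, together with a schedule that implements neither. For non-serious events the protocol promises continuous collection and provides triggered notification. Asymptomatic potassium and liver abnormalities meet no symptom trigger. The loss of mild nausea and diarrhea is conditional on both triggers being required, which the text leaves open.

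The size of the loss cannot be derived from the protocol. The range of 3.9% to 87.1% for at least one event in 40 rests on rates that the protocol attributes to long-term use, so it is an illustration and not a forecast. The 8.8% limit after 0 of 40 needs no assumed rate, but it does need complete recording in 40 treated patients.

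The primary endpoint and the efficacy analyses are unaffected. This is an inexpensive improvement that should be made, not a flaw that invalidates the trial.

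**What to change.** 1. Rewrite section 10 so that it carries out the rule in section 9. State whether the two triggers are alternatives or joint, and define one end of collection that applies to both arms.
2. At the existing 24-hour assessment, ask every patient in both arms the same fixed yes/no items on nausea, vomiting, diarrhea and weakness, whatever the suspected cause or length of stay.
3. Copy potassium and liver values into the study record where routine perioperative blood tests were already taken, in both arms, with no new blood draw.
4. State that any comparison of these events between arms is descriptive.

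The cost is protocol wording, a slightly longer questionnaire at a visit that already takes place, and some transcription of routine results. Laboratory values will be available only where they were taken in routine care, so that part of the record may stay incomplete.

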**11. [Viewing original materials]**

At the conducting medical institution, the principal investigator ensures that all records, including source materials, can be viewed during monitoring, auditing and investigations by accredited clinical research review committees and regulators.

**12. [Method of storing and disposing of samples / information (including materials related to information used in research)]**

The information obtained from this study will be kept strictly until 10 years have passed after all research plans have been completed. Regarding the information obtained at all facilities, all or part of the information that can identify an individual is removed from the personal information and anonymized by numbering. The obtained patient information and questionnaire results will be stored in a locked drawer of the Niigata University Anesthesiology Laboratory in an anesthesiology state and will not be taken out. The correspondence table and patient information will be stored separately, and care will be taken to ensure that information is exchanged between hospitals appropriately. The person in charge of storage shall be [name], the person in charge of research. When discarding the obtained information, shredder the information left on the paper medium and erase the information left in the file format using data erasure software. The results of this research will be published by presenting them at academic meetings such as academic societies and academic journals, but in that case as well, consideration will be given to not being able to identify individuals, and the results of statistical analysis will be the main focus.

If the research is rejected or the research is discontinued after consenting to the research, all the information on the patients to be studied collected up to that point will be discarded and no further data will be collected.

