**5. [Policies for selecting research subjects]**

(1) Research subjects

① Patients aged 20 to 60 years who have been diagnosed with breast cancer and undergo total mastectomy and sentinel lymph node biopsy, or partial mastectomy and sentinel lymph node biopsy at Niigata University Medical and Dental Hospital or Niigata Prefectural Cancer Center Niigata Hospital

② Patients who received written and oral explanations regarding this study and showed their consent to participate in writing.

(2) Exclusion criteria

① Patients with preoperative condition classification (ASA-PS) 4 or higher by the American Society of Anesthesia

② Patients with BMI (Body Mass Index ≥ 30)

③ Patients who already have pain that requires oral painkillers somewhere in the body except for the primary disease

④ Those who are allergic to the drug used

⑤ Persons with hypokalemia

⑥ Patients taking anti-anxiety drugs and antipsychotic drugs

⑦ Patients who are already taking painkillers including opioids

⑧ Patients who have already taken some Chinese medicine

⑨ Patients who have difficulty communicating (dementia, mental retardation, mental illness, do not understand Japanese, etc.)

⑩ Other patients who are judged to be inappropriate by the principal investigator and the investigator

(3) Cancellation criteria

① When the research subject offers to decline participation in the research or withdraws consent

② When the entire research is canceled

③ When the result of intraoperative sentinel lymph node biopsy is positive and axillary lymph node dissection is performed

④ When the person in charge of research determines that it is appropriate to discontinue the research for other reasons.

(4) Voluntary research cooperation and freedom of withdrawal

Participation in the study is decided by the patient's free will, and it is possible to withdraw participation at any time. If the patient withdraws from the study before the start of oral administration, it will be excluded from this study. Patients who refuse to take the second dose after the first dose and withdraw from the study are also excluded from this study. Explain that withdrawal of research participation does not result in any disadvantage in subsequent treatment.

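### Section 12 discards all data, safety data included, when a patient refuses or is discontinued after consent, which conflicts with the continuous adverse-event collection required in section 9

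*Protocol*

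**What the plan says.** The discard rule stands in Protocol section 12, on storing and disposing of information. Its trigger is "If the research is rejected or the research is discontinued after consenting to the research", and its consequence is that "all the information on the patients to be studied collected up to that point will be discarded and no further data will be collected". No category of data is exempted. The same section sets a retention period of 10 years after completion, with no stated exception for patients who stop.

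Section 9, on burden and risk, says: "The collection period for adverse events should be continuous from the acquisition of consent to the end of the study". Section 10 adds that, for complications, "the progress of clinical symptoms and test results is observed and recorded" up to discharge.

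Section 5 describes who may stop. Under freedom of withdrawal: "Patients who refuse to take the second dose after the first dose and withdraw from the study are also excluded from this study". The cancellation criteria include "When the result of intraoperative sentinel lymph node biopsy is positive and axillary lymph node dissection is performed" and "When the person in charge of research determines that it is appropriate to discontinue the research for other reasons".

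Section 13 requires a prompt written report of any serious adverse event that comes to the team's attention. Section 4 lists salivary amylase as the primary endpoint and HADS, STAI, QOR and pain VAS as secondary endpoints. No adverse-event endpoint is listed.

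**The concern.** Two sections give opposite orders about the same records. A site that follows section 12 destroys adverse events that section 9 told it to collect. A site that follows section 9 keeps records that section 12 told it to destroy. Different sites or staff could resolve this differently, and the final report would not show which rule was applied.

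The loss need not be even between arms. Controls take no study drug, so a patient who has one dose, declines the second and leaves can arise only in the intervention arm. Poor tolerability is one possible reason for declining. Removing such records can only lower the adverse-event count in the treated group, and that count is the only evidence on tolerability that this trial will itself produce.

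**Working it through.** The protocol gives no figure on this point to reproduce, so the check is a comparison of texts followed by an illustration.

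**Comparison of the texts**

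| Question | Section 12 | Elsewhere |
| --- | --- | --- |
| Are events recorded before stopping kept? | No, everything is discarded | Implied yes: section 9 collects from consent onwards; section 12 itself retains for 10 years |
| Does collection go on after stopping? | No | Yes, if the study's end in section 9 means the end of the whole trial; section 10 observes complications to discharge |
| Is there an exception for safety data? | None stated | Section 13 secures a written report, for serious events only |

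The first row conflicts on any reading. The second depends on what section 9 means by the end of the study, which the protocol does not define. If it means the end of a patient's own participation, the conflict over further collection with section 9 disappears, but the destruction of events already recorded remains.

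**Who is affected.** Section 12 names refusal and discontinuation as separate triggers, and the second cancellation criterion quoted above uses the same idea of discontinuing. The natural reading therefore covers the investigator-decision and axillary-dissection criteria as well as withdrawal of consent. The wording does not settle it.

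**Illustration of the loss.** Inputs:
- treated patients: 40 (section 4 expects about 40 per group);
- true event rate *p*: 5%, the top of the package-insert range quoted in section 9, with 1% and 0.1% as lower values;
- share *w* of affected patients who stop and are discarded: not given in the protocol, so 0, 0.25, 0.5 and 1 are assumed.

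Formulas, with patients taken as independent:
- expected events retained = 40 × *p* × (1 − *w*);
- chance that at least one event is retained = 1 − (1 − *p*(1 − *w*))^40.

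For *p* = 0.05:
- with *w* = 0, 40 × 0.05 = 2.0 events are expected and 1 − 0.95^40 = 0.87;
- with *w* = 0.5, 40 × 0.025 = 1.0 event is retained and 1 − 0.975^40 = 0.64. The rate among retained patients is 0.025 / (1 − 0.025) = 2.6%, against a true 5%.

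| *p* | Events expected | *w* = 0 | *w* = 0.25 | *w* = 0.5 | *w* = 1 |
| --- | --- | --- | --- | --- | --- |
| 5% | 2.0 | 0.87 | 0.78 | 0.64 | 0 |
| 1% | 0.4 | 0.33 | 0.26 | 0.18 | 0 |
| 0.1% | 0.04 | 0.039 | 0.030 | 0.020 | 0 |

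The last four columns give the chance that at least one event is retained. At the lower rates few events are expected in the first place, so usually nothing is there to lose.

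**The case against.** The best case against the point has several parts.

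- **Serious events are protected.** A reader might infer that patients who stop leave no trace and that serious reactions could never be checked. The protocol does not support this. Section 13 requires a written report of serious events and exempts no one who has stopped. Section 11 keeps source material open to monitors, auditors and regulators, and nothing says that hospital charts are destroyed. This part stands: the loss is of non-serious events and of the study records behind any report.
- **No safety comparison is planned.** A reader might infer that a planned comparison of the arms is biased. Section 4 lists no adverse-event endpoint or test, and the remark in section 6 about few side effects is background on the drug. This stands too. What is affected is the completeness of safety reporting.
- **The trigger may be narrower.** In translated text, the pairing with refusal could mean only the patient's own withdrawal. That is possible. The rule would still reach the patient who withdraws after one dose.
- **Section 10.** A reader might infer that complications are passed on only when the hospital stay is prolonged. The sentence is garbled and may list two separate triggers, so no conclusion is drawn from it.
- **The effect may be tiny.** Section 9 regards side effects as highly unlikely after two doses, and the window for declining the second dose is short. A reader might picture 2 of 40 turning into 0 of 38. That needs the highest quoted rate and every affected patient stopping, and the protocol gives no stopping share. It is a worst case, not an estimate.

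None of these removes the conflict over events already recorded.

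**Conclusion.** The point holds in a limited form. Sections 9 and 12 contradict each other. Followed as written, section 12 would erase adverse events already on record, mainly non-serious ones, together with the study data behind them. At least one affected group, patients who withdraw after a single dose, can exist only in the intervention arm, so the trial could understate events in treated patients.

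The rule should not be described as removing only drug-related stoppers. It also removes controls who withdraw and, on the wider reading, patients cancelled for axillary dissection, which has nothing to do with the drug.

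The size cannot be fixed from the protocol. If half of affected patients stop, the chance of retaining at least one event falls from 0.87 to 0.64 at a 5% event rate and from 0.33 to 0.18 at 1%. These figures assume 40 treated, independent patients, and discarding of every affected patient who stops. The contradiction itself rests on no figure. It is worth correcting because retention is fixed in this document, and no later analysis plan can recover destroyed records.

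**What to change.** Reconcile sections 9 and 12 by changing section 12:

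- Data collected before discontinuation, adverse events in particular, are kept, and adverse events are reported by arm for all randomised patients whatever the reason for stopping, unless the patient explicitly withdraws consent to use of the data.
- The text states which events trigger any discarding: withdrawal of consent only, or also investigator decision and axillary dissection.
- The text states whether adverse-event collection continues after discontinuation, and section 9 defines the end of the study for this purpose.
- The consent text is brought into line.

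The cost is wording in the protocol and consent form, with no extra patients. The one real constraint is that, if patients already enrolled were promised that their data would be discarded, that promise must be honoured and the number affected reported by arm.
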